### Activities in both intervention and control groups

The overview of the study will be presented to all participating prenatal clinics. The problem of smoking during pregnancy and the current national guidelines will be presented. We consider this presentation necessary to introduce the study and ethically justified to ensure that all providers have the same chance to know the importance of the problem and current national recommendations. In a previous clinical trial, this kind of activity was not likely to produce significant changes in providers’ behaviors [28].

### Measurement methods

#### Women’s outcome measurement

The frequency of women receiving the “5 A’s” at the end of pregnancy (primary outcome) and the frequency of women who smoke at the end of pregnancy (secondary outcome) will be measured in a survey conducted within the first 24 hours after delivery, during each woman’s hospital stay. Additionally, tobacco status among women who quit will be validated by cotinine analysis of saliva submitted within the first 12 hours postpartum.

##### Description of questionnaire to women

The survey will be conducted using a questionnaire in paper format that will include a set of core questions, including: basic demographic data (to be extracted from the clinical record); knowledge and attitudes regarding tobacco; tobacco use behaviors (specifically in the last two weeks before delivery); secondhand smoke exposure; and tobacco cessation counseling received during prenatal care. Questions on tobacco use and secondhand smoke exposure will be based on the previously validated questionnaire to assess tobacco use during pregnancy conducted in Argentina and Uruguay and other countries in 2005 [3,4]. Questions on tobacco cessation counseling received during prenatal care will cover the five steps of the “5 A’s” intervention: all women will be questioned as to whether they were asked their smoking status; smokers before pregnancy will be questioned as to whether they were advised to quit; women who smoked before pregnancy will also be asked if they were assisted in their attempt to quit by receiving skills and materials for tobacco cessation and if their counseling was monitored at every prenatal visit.

##### Questionnaire administration

The questionnaire was designed for face-to-face verbal administration by trained interviewers. Interviews will be conducted during the hospital stay after delivery. The questionnaire will take approximately 5–15 minutes to complete.

##### Cotinine analysis

We will measure cotinine levels in saliva during the immediate postpartum period, no later than 12 hours after delivery. A witnessed sample of saliva will be collected only in women that declared during the survey that they used to smoke but that they quit at some time during pregnancy. The sample will be collected by asking women to gently chew a Salivette sponge for 1–2 minutes until they feel it is saturated with saliva. The sponge will be put in a collection tube and stored for further analysis. This analysis will show if they were exposed to nicotine during the past several days. After the analysis is complete, the saliva sample will be thrown away according to biosafety procedures and will not be used for any purpose other than as previously stated. Samples will be kept in freezers and identified with the participant study number and shipped at the end of the collection period following all biosafety international requirements. Analysis of cotinine will be done by the Division of Laboratory Sciences of the Centers for Disease Control and Prevention in Atlanta, Georgia, USA, using gas chromatography and a pre-screening with an ELISA test.

Cotinine clearance has been reported to be higher in pregnancy, leading to a shorter half-life [43]. However, cotinine levels increase with gestational age and are more than twice as high at term than in the first and second trimesters [43].

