### Tobacco use during pregnancy in Argentina and Uruguay

Pregnant women are a priority population for tobacco control efforts because cigarette smoking during pregnancy poses serious risks to fetal health. Smoking during pregnancy may cause preterm delivery, low birth weight, and sudden infant death syndrome [2,9]. Maternal tobacco use is also likely to expose infants and children to secondhand smoke (SHS) and to provide a role model for children’s use of tobacco [3].

There is scarce information on the prevalence of tobacco use during pregnancy in LMIC. Our group conducted the only published survey in Argentina and Uruguay designed to study pregnant women in prenatal clinics, which was part of a global survey performed in nine LMIC [2]. The survey, conducted during 2005 and 2006, showed that tobacco use during pregnancy is culturally acceptable in these countries and found rates of smoking during pregnancy of 10.3% in Argentina and 18.3% in Uruguay. The observed rates were lower for other Latin American countries like Brazil (6.1%), Ecuador (0.8%), and Guatemala (0.8%).

Reports from routinely collected data in a perinatal network of 30 public maternity hospitals attending approximately 90,000 deliveries per year in the Province and City of Buenos Aires in 2008 showed 15% of women reporting smoking at their first prenatal visit [10]. Similar reports from the largest public maternity hospital in Uruguay (Hospital Pereira-Rossell), attending 9,000 childbirths per year (15% of total births in the country), showed that the prevalence of women smoking more than 5 cigarettes per day during pregnancy was 19.5% in 2007 (Internal Report, Informatic Perinatal System, personal communication, [name]).

Magri et al. reported a 33% prevalence of smoking during all pregnancies in a survey performed of 900 women after delivering in Hospital Pereira-Rossell [11]. Cotinine in meconium was tested in a sample of 10% of newborns, and positive determinations reached 51% [11].

The National Observatory of Gender and Reproductive and Sexual Health 2008 conducted a survey during postpartum stays in a sample of 564 women who underwent childbirth in public and private health institutions in Uruguay. Prevalence of smoking during pregnancy was 22% in this sample of women, and 77% reported not receiving systematic counseling interventions from their providers [12].

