### Evidence-based interventions for smoking cessation during pregnancy: the “5 A’s” strategy

A strong body of research supports that clinicians should consistently identify tobacco users and provide tobacco dependence counseling to patients who use tobacco. Brief cessation counseling interventions based on the “5 A’s” model (Ask, Advise, Assess, Assist, Arrange) have been proven effective to increase smoking cessation in a wide variety of settings, populations, and by all types of providers. The “5 A’s” strategy is currently considered the standard of care in the United States of America for all patients contacting clinicians, including pregnant women during prenatal care [13].

Specifically in pregnancy, randomized-controlled trials of brief cessation strategies based on the “5 A’s” have been summarized in several systematic reviews [13,14]. The reviews included 8 [13] to 16 studies [14] and reported a summary risk ratio of 1.7-1.8, with 95% confidence intervals (CI) of 1.3 to 2.2. These findings suggest a 70%-80% improvement in cessation rates in women receiving brief counseling, with a 95% confidence that there is at least a 30% improvement in cessation. The Cochrane review [15], which classified the interventions in a different way, found that women receiving cognitive behavior interventions showed a 5% (95%CI 3%-8%) absolute reduction in the number who continued smoking. The intervention has been proven effective in different ethnic groups (African Americans and non-Hispanic whites) and has been delivered by different types of trained health providers, including physicians, midwives, and nurses. It is also effective among individuals with low socioeconomic status or limited formal education (odds ratio [OR] = 1.42; 95%CI 1.04–1.92) [13]. The “5 A’s” intervention currently recommended for pregnant women is summarized in Table 1[14].

**Table 1 T1:** “5 A’s” Intervention

**Step 1: ASK**	Ask the patient about her smoking status:
	A. I have **NEVER** smoked, or I have smoked less than 100 cigarettes in my lifetime.
	B. I stopped smoking **BEFORE** I found out I was pregnant, and I am not smoking now.
	C. I stopped smoking **AFTER** I found out I was pregnant, and I am not smoking now.
	D. I smoke some now, but I cut down on the number of cigarettes I smoke **SINCE** I found out I was pregnant.
	E. I smoke regularly now, about the same as **BEFORE** I found out I was pregnant.

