### Limitations

The cotinine analysis will allow us to prevent differential non-disclosure of tobacco status between women who declared that they quit smoking at some time during pregnancy in the intervention and control clinics, which can bias the effect estimation on the smoking prevalence [46]. However, it is possible that by assessing cotinine after delivery, we may not detect some women smokers who had not smoked in the last 3–4 days because of labor, delivery, and hospital admission, who also did not self-report smoking. These potential false negative results may pose a limitation in correctly estimating the real prevalence of smokers across all clinics, but will not alter the estimation of the effect of the intervention strategy.

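### Cotinine checks only women who say they quit during pregnancy, so a counselling-related shift into other non-smoker answers could bias the smoking effect undetected

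*Protocol article*

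**What the plan says.** Under Women's outcome measurement, the protocol measures smoking at the end of pregnancy in a postpartum survey and adds that "tobacco status among women who quit will be validated by cotinine analysis of saliva". The Cotinine analysis section fixes who is sampled: saliva is "collected only in women that declared during the survey that they used to smoke but that they quit at some time during pregnancy". No section provides for testing any other self-reported non-smoker during the two outcome data collection periods.

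Limitations accepts that differential non-disclosure can bias the effect on smoking prevalence. It says that cotinine "will allow us to prevent differential non-disclosure of tobacco status between women who declared that they quit smoking at some time during pregnancy". The one residual problem it discusses is a negative cotinine result in a smoker who abstained around delivery. It says such false negatives may distort the prevalence estimate, "but will not alter the estimation of the effect of the intervention strategy".

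Statistical analysis tests the smoking hypothesis with the woman as the unit, by GEE, through the intervention-by-time interaction. Sample size assumes that smoking goes from 18% to 17% in control and from 18% to 12% under the intervention.

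**The concern.** The outcome is a proportion of all women, while the biochemical check covers one group of self-reported non-smokers. A woman who smoked to term can be counted as a non-smoker in three ways: by saying she quit during pregnancy, by saying she stopped before it, or by saying she never smoked. Only the first leads to a saliva sample.

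The arms differ in what could move women between these answers. Intervention clinics aim to ask every patient about smoking and advise smokers firmly to quit; control clinics carry on as usual. The outcome is then a face-to-face self-report in hospital. If the intervention makes some smokers less willing to admit having smoked at all, reported prevalence falls in that arm although nobody has quit, and the fall appears in exactly the interaction that is tested.

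Neither of the other safeguards covers this. The baseline survey addresses under-reporting that is stable over time, not a change brought about by the intervention. The pilot comparison of saliva cotinine with self-report takes place before the intervention, so it cannot show a difference between arms that the intervention causes.

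**Working it through.** **Inputs.** From Sample size: per arm and time point, 7 × 200 + 3 × 120 = 1,760 women; intra-cluster correlation 0.05 both within and between periods; two-sided 5% level; smoking 18% to 17% (control) and 18% to 12% (intervention); stated power 0.89. Assumed, because the protocol gives no value: f, the share of intervention-arm smokers, in excess of control, who give an untested non-smoker answer at follow-up.

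**Step 1: reproduce the stated power.** Because the two correlations are equal, the cluster effect cancels in the pre/post change and leaves a factor of 1 − 0.05. On the log-odds scale:

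- D = [logit(0.12) − logit(0.18)] − [logit(0.17) − logit(0.18)] = −0.407 (OR 0.67)
- SE = √{0.95 × Σ 1/[p(1−p)] / 1,760} over the four proportions = 0.1275
- z = 0.407 / 0.1275 = 3.19; power = Φ(3.19 − 1.96) = 0.89

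This matches the protocol. A simulation with robust GEE standard errors gives 0.887.

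**Step 2: no true effect, only a reporting shift.** Let 17% truly smoke in both arms at follow-up. Reported prevalence in the intervention arm is then 17% × (1 − f), and the false fall is 17 × f points. The last column applies the Step 1 formula.

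| f (assumed) | False fall, points | Apparent OR | Chance of a significant result |
|---|---|---|---|
| 0 | 0 | 1.00 | 0.05 |
| 5% | 0.85 | 0.94 | 0.08 |
| 10% | 1.7 | 0.88 | 0.17 |
| 15% | 2.55 | 0.83 | 0.34 |
| 20% | 3.4 | 0.77 | 0.56 |
| 29% (5/17) | 5.0 | 0.67 | 0.89 |

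Simulating the GEE with a small-sample correction gives similar values: 0.17 at 10%, 0.51 at 20% and 0.84 at 29%. Cotinine as planned would reclassify none of these women.

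**Step 3: what a check on earlier smoking could detect.** Suppose every shifted woman also denies smoking before pregnancy, or when she learned of it. The points lost are then the same, taken from a different base. The protocol does not give that base for the surveyed women. I assume 30%, with 26% to 33% as the range, borrowing the rates for women in the Background. With p = 0.30 in three cells and 0.30 minus the shift in the fourth, the Step 1 formula gives:

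- shift of 1.7 points: D = −0.082, SE = 0.102, power 0.13 (0.12 to 0.14 over the range)
- shift of 5 points: D = −0.251, SE = 0.103, power 0.69 (0.66 to 0.73 over the range)

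The check can therefore reveal a large shift but will often miss a small one.

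**The case against.** The strongest reply is that the shift is assumed. Nothing in the protocol shows it, and a woman repeatedly counselled as a smoker might just as well claim falsely that she quit, which is the answer that is tested. Interviewers are independent of the clinics, and under-reporting that is equal across arms and periods would mainly dilute the effect. All this stands: the point is an open route to bias, not a demonstrated one, and the table in Step 2 is a what-if.

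Three stronger readings are tempting but not supported.

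- A reader might infer that Limitations claims cotinine protects the whole effect estimate. It does not. The claim is confined to declared quitters, and the statement that the effect is unaltered refers to false-negative cotinine results. What is missing is an acknowledgement of the untested women.
- A reader might take the Background figures (33% self-reported smoking; "Cotinine in meconium was tested in a sample of 10% of newborns, and positive determinations reached 51"%) as the scale of the bias. They suggest local under-reporting. But passive exposure may contribute, only a subsample was tested, and they say nothing about a difference between arms.
- A reader might map the testing rule onto the Table 1 answers, such as never having smoked or stopping before finding out about the pregnancy. Table 1 is the providers' script; the outcome comes from a separate questionnaire. The second answer can also include women who quit in early, unrecognised pregnancy, who would be tested.

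It is also fair to say that targeted testing is an openly stated choice, and that sampling more groups means an extra procedure for more women. Extending it only to women who report stopping earlier would still leave denial by self-reported never-smokers untested.

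**Conclusion.** The concern holds as a gap in protection for one secondary outcome. Saliva testing covers declared in-pregnancy quitters only, while the effect is estimated on prevalence among all women. An intervention-related shift of true smokers into the other non-smoker answers would favour the intervention, and the cotinine test, the baseline survey and the pilot could not reveal it.

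The size is unknown. If 17% truly smoke in both arms and there is no real effect, an excess of 10% of intervention-arm smokers in untested answers gives a false 1.7-point fall and raises the chance of a significant result from 0.05 to about 0.17. An excess of 29% is needed to mimic the full 5 points. These figures rest on the assumed excess and on the protocol's own design values. They do not show that the bias will occur.

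**What to change.** 1. Pre-specify the same GEE intervention-by-time contrast on the proportion of women who report that they smoked before pregnancy, or at the time they learned of it. Take the categories from the outcome questionnaire, not from Table 1. Of the two, smoking when she learned of the pregnancy is more useful if the questionnaire records it, because it also catches women who falsely say they stopped earlier. Report the estimate with its 95% CI beside the smoking result.

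2. State how it will be read. Prenatal counselling cannot change this status, so a fall in the intervention arm relative to control points to differential denial, chance or a change in case mix. The smoking result should then be described as possibly due to reporting and not claimed as cessation without qualification. Given the limited power in Step 3, a non-significant result must not be read as excluding the bias.

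3. Add one sentence to Limitations: women who report never smoking or stopping before pregnancy are not tested, so cotinine does not protect the prevalence effect as a whole.

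The cost is one extra analysis, since the survey already identifies women who smoked before pregnancy, and a few lines of text. Extending saliva sampling to further groups is optional and not part of this fix.

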### Attitude and readiness to change

We will assess the attitudes and readiness to provide counseling for smoking cessation to women (secondary outcome) following the “5 A’s” intervention in all prenatal care providers working at participating prenatal clinics. To that purpose, a self-administered questionnaire will be designed, adapted from a questionnaire developed and used by our group to evaluate birth attendants’ readiness to change in the Guidelines Trial [28].

#### Process measures

Process data will be collected during the intervention period at prenatal clinics included in the intervention group. The objectives of this process evaluation are to: 1) detect implementation problems that could be causal, in case the intervention was not effective; and 2) facilitate the replication of the intervention, in the event that it is proven effective. Twice during the intervention period (at the mid-way point and at the end of period), an external observer will monitor if the smoking cessation program is implemented and how it is organized.

#### Data collection and management

Outcome data will be collected in two six-month periods at all participating prenatal clusters: a baseline period and a follow-up period, separated by the intervention phase during which no outcome data will be collected. During the six-month data collection periods we will collect data on ≥200 women who have received prenatal care at each of the participating clinics. Outcome data will be collected in the maternity hospitals where women attending prenatal care at the participating prenatal clinics deliver. Process data will be collected during the intervention phase and only at intervention prenatal clinics.

Trained interviewers, independent of the participating prenatal clinics, will be responsible for the administration of the questionnaire to women, including obtaining the saliva samples. To allow for interviewing women within the first 12 hours after deliveries, two shifts of interviews will be organized: one in the morning and another in the evenings. The interviewers will identify all consecutive women who have undergone childbirth in the past 12 hours and who have received prenatal care at any of the participating prenatal clinics. After obtaining informed consent, they will interview each woman and obtain the saliva sample (if the woman is eligible). Demographic and childbirth data will be extracted from the clinical record. Cotinine samples will be kept refrigerated and then frozen in order to keep them in the appropriate conditions until shipment to CDC for analysis. This postpartum strategy for data collection has been proven feasible and successful in previous studies of our group [35,36].

Data will be collected on paper forms designed specifically for the study. A digital image of the interview form will be taken and sent to the local data center for data entry, but the inclusion form and the hard copy of the interview form will remain at the hospital until the end of the data collection period. With this system, it is ensured that personal identifiers will not be taken from the hospital and will be kept securely by the hospital staff.

The data forms will be entered in each country in a secure web data management system called OpenClinica, which is an open source software for clinical research studies using distributed data entry [44]. Digital pictures of the data forms will be sent encrypted to the data center by email. This system will allow for a digital backup of all study data forms, as well as a parallel second data entry of 10% of the forms to detect systematic errors at data entry. This method has been successfully used in other studies by our group.

### Statistical analysis

To test the primary hypothesis, we will consider the clusters of prenatal clinics as the unit of analysis. We are interested in observing how the absolute difference of the percentage of women who received the 5 A’s differs between the control and the intervention group. For that reason, we will compute the outcome rate for each prenatal clinic at baseline and the follow-up periods, and then we will calculate the outcome rate change as the difference between the follow-up and baseline rates. We will apply the *t*-test to those differences in order to test the intervention effect. It has been demonstrated that the *t*-test for two samples applied to cluster rates is appropriate when the number of clusters is low [45].

For the second hypothesis, we will use the woman as the unit of analysis because we want to study the effect of the intervention on the individual. For that we will fit a model in which the variables included will be the intervention, the time (baseline and follow-up measures) and the “intervention by time” interaction. To test the effect of the intervention we will focus on the significance of the interaction. We will use a Generalized Estimation Equation (GEE) to estimate the model and we will report the effect size as OR with the 95% confidence interval. For both outcomes, we will perform an intention-to-treat analysis to compare the groups.

To test if the intervention has changed the attitudes and readiness of midwives towards providing counseling to women, we will consider the percentage of providers that reported they are planning to change their approach about tobacco with their patients in the following six months or they have already changed it in the last six months. We will use the same analytical approach that will be used for the primary hypothesis.

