### Randomization procedures

The conformation of the cluster will be different in each country. Thus, we will consider the following as a cluster: groups of prenatal clinics, composed by the prenatal clinic located inside the maternity hospital and the associated prenatal clinics located in the primary health centers of the area. Deliveries are assisted at the hospitals in both countries. Thus, the outcome will be assessed at the hospitals.

For cluster randomized trials with repeated cross-sectional binary measurements and a limited number of clusters, it is important to attempt to achieve as much balance as possible between the two arms of the study [31]. Based on the results of the initial assessment of health facility characteristics in the start-up phase of the study and using the baseline data, a “balanced randomization” technique [32] will be used to better achieve balance between the treatment groups in terms of the following characteristics of the prenatal clinics: frequency of women receiving the “5 A’s,” frequency of women who smoke during pregnancy, number of health providers/annual number of deliveries, proportion of midwives or nurse midwives who attend prenatal care/total of providers, and country. We have used similar randomization procedures in our recently published trial of a behavioral intervention to improve obstetrical care [28].

The analysis of the baseline data and the balanced randomization procedure will be performed by the study statistician, who will not be involved in the project management. Thus, there will be a clear separation between the generator of the intervention assignment and the study coordination [32].

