### Sample size

The sample size is based on both primary and secondary objectives. A pre-test post-test (2 time–points) nested cross-sectional design was planned with 10 intervention and 10 control clinics. Each intervention and control group will contain seven clinics, with a minimum of 200 women at each time point, and three smaller clinics, with a minimum of 120 women at each time point. For each objective, the statistical power was estimated using a Monte Carlo simulation with 3,000 repetitions. In the simulation, binary outcomes from women were generated from the proposed pre-test post-test nested cross-sectional design under the following assumptions:

• An increase in the frequency of women receiving the “5 A’s” at the end of pregnancy from 10% to 20% in the control group and from 10% to 50% in the intervention group (i.e., an intervention effect of 30%) for the primary objective.

• A decrease in the frequency of women who smoke at the end of the pregnancy from 18% to 17% in the control group and from 18% to 12% in the intervention group (i.e., an intervention effect of 5%) for the secondary objective.

• An intra-cluster correlation between 2 outcomes from different women at different times (pre-test/post-test) = Intra-cluster correlation between 2 different women at the same time of 0.05. The value of the latter intra-cluster correlation coefficient was observed in a study carried out in Argentina and Uruguay [3].

For this sample size, the estimated statistical power at the 5% level of significance (2-sided) is 1.0 for the primary objective and 0.89 for the secondary objective.

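### The allocation is balanced on country, but the primary t-test on cluster change scores leaves country out, so it is conservative if change differs between Argentina and Uruguay

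*Protocol article*

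**What the plan says.** Under Randomization procedures, the protocol article says that "a “balanced randomization” technique [32] will be used to better achieve balance between the treatment groups". The factors are the baseline frequency of women receiving the 5 A's, the frequency of smoking in pregnancy, and "number of health providers/annual number of deliveries, proportion of midwives or nurse midwives who attend prenatal care/total of providers, and country". The stated reason is that clusters are few.

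Under Statistical analysis, the cluster is the unit for the primary hypothesis. A rate is computed for each cluster in each period, "and then we will calculate the outcome rate change as the difference between the follow-up and baseline rates". Then: "We will apply the *t*-test to those differences in order to test the intervention effect". The only justification given is that the t-test suits a low number of clusters. No balancing factor is named as a covariate or stratum, and no randomisation test is mentioned. The provider attitude and readiness outcome is to be analysed in the same way as the primary outcome.

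Participating clusters describes 10 clusters in each country. An Argentine cluster is a maternity hospital with two or three health centres; a Uruguayan cluster is a single clinic.

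**The concern.** A two-sample t-test estimates its error from the spread of cluster changes within each arm, as if any split of the 20 clusters could have been drawn. Balancing rules out the splits in which the countries are unevenly shared between arms. If the countries change by different amounts over time, that difference cancels out of the comparison of arms but still widens the spread within each arm. The standard error is then larger than the real sampling error, and the precision that the balancing was meant to buy does not reach the interval or the test.

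A country difference in change is plausible. The clusters are built differently, and Argentine women move from health centre to hospital at 34–36 weeks while Uruguayan women do not. The investigators themselves chose country as a balancing factor. The document gives no figure for such a difference.

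**Working it through.** **Inputs from the Sample size section.** There are 10 clusters per arm. Per arm and period, 7 of them supply at least 200 women each and the other 3 at least 120 each. Rates go from 10% to 20% in control and from 10% to 50% in intervention. The intra-cluster correlation (ICC) is 0.05 both within and between periods, which means a cluster autocorrelation of 1. The test is two-sided at 5%.

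**Assumptions, not in the document.** Five clusters per country in each arm; a country difference δ in change; an illustrative 10-point effect; an alternative autocorrelation of 0.8.

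**Planned power first.** The mean of 1/m over clusters is (7/200 + 3/120)/10 = 0.006. The variance of one cluster's change has two parts.

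- Sampling part: 0.95 × [p₀(1−p₀) + p₁(1−p₁)] × 0.006. Control: 0.95 × (0.09 + 0.16) × 0.006 = 0.001425. Intervention: 0.95 × (0.09 + 0.25) × 0.006 = 0.001938.
- Cluster part at autocorrelation 1: (√(0.05 × 0.16) − √(0.05 × 0.09))² = 0.0005 for control; (√(0.05 × 0.25) − √(0.05 × 0.09))² = 0.0020 for intervention.

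The SE of the difference is √[(0.001925 + 0.003938)/10] = 0.024. The planned effect of 0.30 is about 12 standard errors, so the stated power of 1.0 is reproduced. Simulation also gives 1.000.

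**Effect of leaving country out, no treatment effect.** Let s² be the variance of a cluster's change within country.

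- True SE = √(2s²/10).
- In each arm five clusters sit at +δ/2 and five at −δ/2. This adds 10(δ²/4)/9 = 10δ²/36 to the within-arm variance that the t-test sees.
- t-test SE = √[0.2 × (s² + 10δ²/36)].

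With δ = 0.10 the added term is 0.002778.

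- Autocorrelation 1: s² = 0.001425 + 0.0005 = 0.001925. True SE = 0.0196; t-test SE = √(0.2 × 0.004703) = 0.0307.
- Autocorrelation 0.8: cluster part = 0.0045 + 0.0080 − 2 × 0.8 × 0.0060 = 0.0029, so s² = 0.004325. True SE = 0.0294; t-test SE = √(0.2 × 0.007103) = 0.0377.

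The t-test threshold (2.101 on 18 df) then corresponds to 2.101 × 0.0307/0.0196 = 3.29 true standard errors in the first case and 2.101 × 0.0377/0.0294 = 2.69 in the second.

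**Simulation** (beta-distributed cluster rates, binomial counts, protocol cluster sizes). Ranges show separate runs.

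| Autocorrelation | δ | t-test SE / true SE | Type I error, t-test | Power for 10 points: t-test / with country |
|---|---|---|---|---|
| 1 (protocol) | 0 | 0.020 / 0.020 | about 5% | 0.98 / 0.98 |
| 1 | 5 points | 0.023 / 0.020 | 2.4% | 0.97 / 0.98 |
| 1 | 10 points | 0.031 / 0.020 | 0.2–0.3% | 0.89–0.90 / 0.98 |
| 1 | 20 points | 0.051 / 0.021 | about 0 | 0.35–0.36 / 0.98 |
| 0.8 (assumed) | 0 | 0.029 / 0.030 | about 5% | 0.83 / 0.83 |
| 0.8 | 10 points | 0.038 / 0.030 | 1.2–1.4% | 0.67–0.70 / 0.82–0.84 |
| 0.8 | 20 points | 0.055 / 0.030 | about 0 | 0.29–0.30 / 0.83–0.84 |

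With country in the model, type I error is about 5% in every row. Power for the 30-point effect is 1.0 in every row, with or without country.

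**Is the restricted allocation the cause?** With autocorrelation 1 and δ = 10 points, simple randomisation gives SE 0.030 against a true 0.030 and type I error of 5.0%. Keeping only the best-balanced 10% of allocations (an assumed cut-off) on country and baseline rate gives 0.031 against 0.019 and 0.2%.

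**Other factors.** If five balancing factors together explain 0, 10, 25, 50 or 75% of the variance of change, the unadjusted type I error is 4.3, 4.5, 3.1, 1.2 or 0.5%.

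**The case against.** A reader might infer that the analysis ignores every balancing factor. It does not: the baseline 5 A's rate enters through the subtraction. Differencing also cancels any stable difference in level due to country, staffing or smoking rate. Only a difference in change survives.

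A reader might also infer that the error rate is wrong in the damaging direction, or that the primary conclusion is at risk. Neither is supported. The departure is conservative, it arises only if a balancing factor predicts change, and the planned effect is large enough that power stays 1.0. The Sample size section assumes one control change for all clinics. Around that mean rise of 10 points, a 20-point gap means a rise of 0 in one country and 20 in the other, which is extreme. At a 5-point gap the loss is small. The 10-point effect is illustrative and appears nowhere in the document.

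It is also tempting to say that subtracting the baseline is itself a mistake and that it should be a covariate. That does not give a consistent gain: at autocorrelation 0.8, power was 0.81 for the covariate version against 0.83 for subtraction.

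These limits all stand. What remains is that the article names the primary test outright, so this is a stated choice and not a detail left to an analysis plan. Having few clusters justifies a t-test, but it does not address restricted allocation.

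**Conclusion.** The point holds as a conditional loss of precision. The design restricts allocation by country and the stated primary test does not use it. If change differs by 10 points between countries, with five clusters per country in each arm, the standard error is about 1.5 times too large under the protocol's ICC (0.031/0.020) and about 1.3 times at an assumed autocorrelation of 0.8 (0.038/0.030). If change does not differ by country, nothing is lost.

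The size rests on the assumed country split, country difference and autocorrelation. The planned 30-point result is safe. The practical cost is an over-wide interval around the absolute difference and lower power for effects well below 30 points. The same applies in principle to the readiness outcome, for which the article states no effect size or power; its loss cannot be quantified from the document.

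**What to change.** Replace the two-sample t-test by a linear model of the cluster change scores with arm and country, using a t reference on 20 − 3 = 17 degrees of freedom. Alternatively, use a permutation test over the set of allocations that met the balance criterion; this reflects all five factors without spending degrees of freedom, but the admissible set must be kept from the randomisation. State the same method for the provider-readiness outcome.

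The cost is a change of wording before analysis and one degree of freedom. The critical value moves from 2.101 to 2.110, and with no country difference power is unchanged to two decimals (0.98 and 0.98; 0.83 and 0.83). Using the baseline rate as a covariate instead of subtracting it is optional and not needed for this correction.
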